## Abstract

Gait disorders are the most frequent symptoms associated to multiple sclerosis (MS). Robot-assisted gait training (RAGT) in people with MS (PwMS) has been proposed as a possible effective treatment option for severe motor disability without significant superiority when compared to intensive overground gait training (OGT). Furthermore, RAGT at high intensity may enhance fatigue and spasticity. This study aims to evaluate the effects of a low-intensity RAGT at progressively increasing intensity compared to conventional RAGT and OGT in PwMS and moderate to severe walking impairment. 24 PwMS will be recruited and assigned to one of the three treatment groups: low-intensity RAGT at progressively increasing intensity, conventional RAGT and OGT. All participants will receive 3-weekly treatment sessions of 3 hours each for 4 weeks. In the first 2 hours of treatment, all participants will receive a rehabilitation programme based on stretching exercises, muscle strengthening and educational interventions. During the last hour, subjects will undergo specific gait training according to the assignment group. Outcomes will be assessed before and after treatment and at 3-month follow-up. The primary outcome is walking speed. Secondary outcomes include mobility and balance, psychological measures, muscle oxygen consumption, electrical and haemodynamic brain activity, urinary biomarkers, usability, and acceptability of robotic devices for motor rehabilitation. The results of this study will provide a safe, affordable and non-operator-dependent, intervention for PwMS. Results in terms of functional, psychological, neurophysiological and biological outcomes will confirm our hypothesis. The study’s trial registration number: NCT06381440.

WHAT IS ALREADY KNOWN ON THIS TOPICGait disorders are frequent in people with multiple sclerosis (PwMS) frequently associated with a progressive decline in cardiorespiratory fitness. Robot-assisted gait training (RAGT) represents an effective treatment option, allowing the reproduction of physiological gait patterns. Different combinations of gait parameters within the rehabilitative intervention may result in various degrees of metabolic engagement and disability reduction.WHAT THIS STUDY ADDSThe PROGR-EX study aims to investigate whether the variability of response to RAGT in PwMS might be related to the imposed load factors and the consequent metabolic response. It explores the response to low-intensity RAGT at progressively increasing intensity regarding functional, psychological, neurophysiological and biological outcomes.HOW THIS STUDY MIGHT AFFECT RESEARCH, PRACTICE OR POLICYThe PROGR-EX study would optimise using RAGT in future research studies and clinical practice, identifying a non-operator-dependent intervention model. Identifying the optimal dose response could help treat PwMS, where fatigue management must be considered in the definition of the rehabilitation intervention.

## Introduction

Multiple sclerosis (MS) is a demyelinating neurodegenerative disease involving the central nervous system through a chronic autoimmune inflammatory process,^1^ affecting 2.9 million people worldwide in 2023.^2^ Gait disorders are the most frequent symptoms, and it is estimated that approximately 50% of patients require walking assistance within 15 years from symptom onset.^3^ The high prevalence of motor dysfunction and gait disability in people with MS (PwMS) is often associated with a progressive decline in cardiorespiratory fitness, placing them at increased risk of cardiovascular events.^4 5^

The approaches focusing on gait rehabilitation help reduce the patient’s disability and improve activity and independence.^6^ The use of robotic devices for gait rehabilitation has been widely documented in neurological disorders,^7–10^ and robot-assisted gait training (RAGT) in PwMS has been proposed as a possible effective treatment option for severe motor disability to address the specific impairments of gait and balance disorders in MS.^11 12^ Robotic devices such as walking exoskeletons make it possible to support movements involved in walking, reproducing physiological gait patterns, prolonging the reproduction of task-specific motor skills and reducing the therapist’s physical exertion. Different combinations of gait parameters within the rehabilitative intervention could bring different degrees of metabolic engagement and result in disability reduction. These aspects could be relevant where RAGT continues to prove effective in increasing patient mobility,^12 13^ but without showing significant superiority compared with intensive overground gait rehabilitation,^14^ associated with a wide interindividual response variability.

Straudi *et al* analysed the individual determinants of the imposed load in a sample of PwMS.^14^ The exercise intensity was calculated considering the average training speed of the patients’ basal speed, which was measured with a walking test to obtain an objective parameter for the internal load imposed on the patients. The results showed a great variability for the RAGT group, with a range of relative exercise intensity between 11% and 114%. The comparison between the relative intensity of training and functional outcomes showed that in the RAGT group, there was a significant inverse relationship between the relative intensity of exercise and the increase in walking speed at the end of rehabilitation. Furthermore, considering a minimal clinically important difference for walking speed set at 20%, Straudi *et al* observed that most of the responders were PwMS that walked slower at the pretreatment assessment.^14^ Benefits of low-intensity training at progressively increasing intensity have also been observed in PwMS when empowered by blood flow restriction,^15^ muscular and haemodynamic responses in diseases such as peripheral arterial disease,^16–18^ stroke^19 20^ and dialysis patients.^21–23^

From a neurological point of view, there is limited information regarding the mechanisms of cerebral reorganisation after gait rehabilitation using RAGT. Several non-invasive methods can be used to assess the impact of rehabilitation on neuroplasticity, including functional near-infrared spectroscopy (fNIRS) and electroencephalography (EEG). The fNIRS investigation evaluates the degree of cortical activation by measuring cerebral oxygenation^24^; the EEG evaluates brain activation by detecting cortical electrical activity.^25^ Both techniques present some limitations, but integrating fNIRS and EEG could help overcome the weakness of the single method.

From a biomolecular point of view, identifying a biomarker of MS progression and response to rehabilitation treatment represents a critical point in managing the disease.^26^ microRNAs (miRNAs) have been found in various body fluids, including plasma, cerebrospinal fluid, urine and saliva. It is a small non-coding RNAs that regulate mRNA stability, controlling gene expression.^27^ Changes in their expression have been associated with the development and progression of numerous diseases, suggesting potential clinical applications in MS.^27^ As urine is an extracellular human body fluid obtained in large volumes using simple, non-invasive methods, urinary miRNAs may represent reliable biomarkers of MS progression and response to rehabilitation treatment.

Finally, the patient’s perception of different rehabilitative approaches represents a strong motivational drive in the successful treatment outcome. Therefore, the usability and acceptability of robotic devices for motor rehabilitation must be evaluated.

### Aims of the study

The study’s primary aim is to test whether the variability of response to RAGT in PwMS might be related to the imposed load factors and the consequent metabolic response.

The secondary aims are to investigate MS progression and response to rehabilitation treatment through the study of urinary miRNA and to collect information about the usability, acceptability and perceived pleasantness of new rehabilitative technologies in gait training from the patient’s perspective.

## Methods

### Study design and setting

This is a three-group parallel-assignment pilot, double-blinded, randomised control trial. PwMS who meet the inclusion criteria and provide written informed consent will be assigned to one of the three treatment groups: the low-intensity RAGT at progressively increasing intensity group, the conventional RAGT group or the overground training (OGT) group.

The protocol of this clinical trial is reported following the Standard Protocol Items: Recommendations for Interventional Trials (SPIRIT) guidelines.^28^ A SPIRIT checklist is available as online supplemental material. Subjects will be recruited from the patients afferent to the Outpatient Rehabilitation Clinic at the University Hospital of Ferrara. Enrolment began on 15 November 2023 and is expected to continue until December 2024. Final data are expected to be collected in March 2025, and the study results will be published in about 6 months.

10.1136/bmjsem-2024-002039.supp1Supplementary data

### Selection criteria and recruitment of participants

PwMS will be included if they meet the following inclusion criteria: (a) men and women between 18 and 65 years; (b) diagnosis of MS (primary or secondary progressive) without relapses in the preceding 3 months; (c) disability rate defined by Expanded Disability Status Scale score from 6 to 7^29^; (d) ability to perform the Timed 25-Foot Walk (T25-FW) test^30^ and (e) Mini-Mental Status Examination score ≥24/30.^31^

PwMS will be excluded if they have (a) other (neurological) conditions that may affect motor function; (b) medical conditions might interfere with the ability to complete the study protocol safely; (c) the presence of spasticity with a modified Ashworth Scale (MAS) score >3 or retractions limiting the range of motion of the hip, knee or ankle; (d) MS relapses or medication changes, or any other confounding factors during the study period and (e) rehabilitation treatment or botulinum toxin injection in the 3 months preceding the start of the study.

During the first appointment, potential participants will be informed about all the study procedures and screened following the inclusion criteria. If the inclusion criteria are met, potential participants will be given a study information leaflet detailing the study’s objectives, procedures, time frame, risks and potential benefits, as well as the telephone contact details of the staff involved and the Consent Form. A copy of the Consent Form is available as online supplemental material. In the following 3 days, candidates will be contacted by telephone and asked about their decision. For those who decide to participate, an appointment will be scheduled at which signed informed consent will be requested, and a physiotherapist will perform baseline assessments. The total number of subjects screened will be recorded according to the Consolidated Standards of Reporting Trials guidelines (figure 1).

**Figure 1 F1:**
[figure not shown]
Consolidated Standards of Reporting Trials flow diagram of the study. OGT, overground training; RAGT, robot-assisted gait training.

### Randomisation and blinding

An external administrator will generate and manage the randomisation list, created with the online application available at www.randomization.com. Subjects enrolled will be assigned to one of the three treatment groups through a block randomisation approach. The outcome assessor will be blinded to the subject’s group assignment. All outcome data and group assignments will be organised in separate datasets to maintain blindness during data analysis.

### Intervention

All participants will receive 3-weekly treatment sessions of 3 hours each for 4 weeks and 12 sessions. Patients who miss more than three rehabilitation sessions will be excluded from the study.

In the first 2 hours of treatment, an experienced physiotherapist will propose a programme based on stretching exercises, muscle strengthening and educational interventions. According to the assignment group, subjects will undergo specific gait training during the last hour. The different kinds of walking treatment are graphically represented in figure 2. All interventions will be delivered at the Rehabilitation Clinic of the University Hospital of Ferrara.

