### Sample size calculation

As this is a pilot study, the sample size does not need to be calculated.^55^ The sample planned for this preliminary study comprises 24 subjects, 8 in each intervention group.

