### Intention to treat

The data will be analysed according to intention to treat, although a subsequent per-protocol analysis will be carried out to check the stability of the conclusions. The multiple imputation procedure will be carried out in case of missing data.

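### Post-randomisation exclusions for missed sessions, and for events during the study, are not reconciled with the intention-to-treat analysis and can bias the comparison of arms

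*Protocol article*

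**What the plan says.** Four places in the protocol article bear on this point.

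- **Intervention.** The course is 12 sessions, three a week for four weeks. The attendance rule reads: "Patients who miss more than three rehabilitation sessions will be excluded from the study". It refers to the study, not to an analysis set.
- **Selection criteria and recruitment of participants.** Exclusion criterion (d) is "MS relapses or medication changes, or any other confounding factors during the study period". It stands in the eligibility list but describes events that come later.
- **Intention to treat.** "The data will be analysed according to intention to treat, although a subsequent per-protocol analysis will be carried out" as a check on the conclusions. The section then adds: "The multiple imputation procedure will be carried out in case of missing data".
- **Sample size calculation.** "The sample planned for this preliminary study comprises 24 subjects, 8 in each intervention group". No expected rate of dropout or exclusion is given.

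No section says whether a patient who meets the attendance rule or criterion (d) is still assessed at T1 and at the 3-month follow-up (T2), or belongs to the intention-to-treat set.

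**The concern.** An intention-to-treat analysis compares the groups as randomised. Attendance, relapse and medication change during the study all come after allocation and may be affected by it. Removing patients for these reasons gives up the protection of randomisation.

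The trial's own rationale makes this more than a formality. The Abstract warns that high-intensity robotic training may increase fatigue and spasticity, and the Discussion says that such symptoms may limit how well the intervention works and can be applied. The arms are meant to differ in intensity, so missed sessions could be a consequence of the assigned arm and could also be related to walking outcome. The outcomes of those patients are part of what the trial sets out to learn.

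The last limb of criterion (d), any other confounding factor, is undefined, so it cannot be applied in the same way to every patient.

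**Working it through.** **1. Timing of the two rules**

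- Attendance: 3 sessions × 4 weeks = 12, as the article states. Missing more than three means attending 12 − 4 = 8 or fewer (67%). A patient who attends 9 (75%) stays in. The rule can be triggered only once training is under way, hence after allocation.
- Criterion (d): inclusion criterion (b) already requires no relapse in the 3 months before entry. Criterion (d) therefore adds events after enrolment. The time at risk is about four months (4 weeks of treatment plus 3 months to T2).

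**2. Comparison with the analysis section**

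Intention to treat needs every randomised patient in the assigned arm. Exclusion from the study, read literally, ends their contribution. Rules of this kind normally define a per-protocol set, and the article plans one, but it does not attach the rules to it.

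**3. How often the rules might apply (assumed rates; the article gives none)**

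P(at least one) = 1 − (1 − p)^n

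| Assumed rate p | Expected losses, 24p | P(≥1 of 24) | P(≥1 in an arm of 8) |
|---|---|---|---|
| 5% | 1.2 | 71% | 34% |
| 10% | 2.4 | 92% | 57% |
| 20% | 4.8 | 99.5% | 83% |

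Each exclusion removes 1/8 = 12.5% of an arm.

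**4. Possible size of the bias (illustration)**

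Assumptions: two arms of 8, normal outcomes in SD units, no true difference, losses in one arm only, no imputation. Results are from simulation.

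| Lost from one arm | Worst case: lowest outcomes lost | Correlation 0.5 | Correlation 0.3 |
|---|---|---|---|
| 1 of 8 | 0.20 SD | 0.10 SD | 0.06 SD |
| 2 of 8 | 0.38 SD | 0.19 SD | 0.11 SD |

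The correlation is that between the propensity to be excluded and the outcome. As a check, the shift should be close to the correlation times the worst case: 0.5 × 0.38 = 0.19 and 0.3 × 0.38 = 0.11, as simulated.

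In the worst case, a two-sided 5% t-test with no true effect rejects in about 7.7% of trials after one loss and about 12% after two, against 5.0% with none.

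**5. What imputation could do**

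If the lost outcomes were imputed, the model would have 8 − 1 = 7 or 8 − 2 = 6 observed patients in the affected arm. Standard multiple imputation assumes that outcomes are missing at random given the observed data. Loss through poor tolerance or relapse may break that assumption.

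**The case against.** The strongest reply is that multiple imputation is planned. If exclusion means only that participation stops, and the missing outcomes are then imputed, all 24 patients remain in the main analysis and it differs from the per-protocol analysis. A reader might infer that the intention-to-treat set simply becomes the per-protocol set. The article does not support that, because it neither states nor rules out imputation for these patients. What stands against the plan is that their handling is left open, and that outcomes which could have been measured would be lost by design.

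Other stronger readings also go beyond the text:

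- **That T1 and T2 are never measured after exclusion.** This is the literal consequence of leaving the study, but the article does not say that assessments stop.
- **That criterion (d) is a working procedure for removing patients, applied by staff who know the arm.** It sits in an eligibility list, no removal procedure is described, and nobody is named as applying it. The outcome assessor and the statistician are blinded.
- **That the worst responders would be lost selectively by arm.** This is possible but not shown. The first two of the three hours are the same in every arm, overground training allows rest breaks, conventional robotic training is adapted to the patient, and the Discussion calls robotic training safe and well tolerated. Similar losses across arms would largely cancel in the comparison.

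It is also fair to say that this is a small pilot which disclaims definitive conclusions. That limits the consequences but does not remove the conflict: tests between arms are planned, and the Discussion expects significantly greater change in one arm.

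**Conclusion.** The concern holds as a conflict within the article. The attendance rule removes randomised patients from the study, and criterion (d) names events that arise after enrolment. Both are at odds with the stated intention-to-treat analysis, and no section resolves this. The attendance rule is the firmer half; criterion (d) is at least badly worded for an eligibility criterion.

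The comparison of arms can be biased as a result. Neither the size nor the direction can be determined from the article. The illustrated range, 0.06 to 0.19 SD under moderate correlation and up to 0.38 SD in the worst case, rests on assumed losses of one or two patients in a single arm and on no imputation. It shows what arms of 8 are exposed to and is not a forecast.

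The point should be settled while patients can still be followed, because outcomes that were not collected cannot be recovered at analysis.

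**What to change.** Reconcile the Intervention section, exclusion criterion (d) and the Intention to treat section as follows.

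1. Separate stopping of training from leaving follow-up. Seek T1 and T2 outcomes from every randomised patient who still consents, whatever their attendance or later events.
2. Analyse all randomised patients in their assigned arm in the main analysis.
3. Apply criterion (d), as an eligibility criterion, only to what is known before randomisation. Record later relapse, medication change or other specified events as intercurrent events, and replace the open-ended limb with a defined list.
4. Use the attendance and event rules only to define the per-protocol set.
5. Use multiple imputation only for outcomes that could not be obtained.

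Possible wording for the attendance rule: *Patients who miss more than three sessions are invited to the T1 and T2 assessments and are analysed in their randomised group; they are left out of the per-protocol set only.*

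Whether training continues for such patients is a clinical matter that this change leaves untouched.

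The cost is a protocol amendment and a few extra T1 and T2 visits. Enrolment began in November 2023, so the amendment may fall in a running trial. Any patients already excluded should then be reported by arm with the reason. The planned 24 patients, 8 per arm, do not change.

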**Figure 2 F2:**
[figure not shown]
Graphical representation of the different kinds of walking treatment. OGT, overground training; RAGT, robot-assisted gait training; t, time; v, velocity.

#### Low-intensity RAGT at progressively increasing intensity

Subjects allocated to this group will receive gait rehabilitation on the Lokomat device (Hocoma AG, Volketswil, Switzerland). During the session, subjects will wear a harness connected to a body weight support system and walk on a treadmill guided by an exoskeleton according to a physiological movement pattern. The device will be set at 60% robotic assistance, 50% load suspension and a speed initially set at 1.0 km/hour, with progressive increments of 0.1 km/hour at each training session. The working time consists of bouts of 3 min of work alternated by 1 min of recovery, to be repeated eight times.

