#### Conventional RAGT

Subjects allocated to this group will receive gait rehabilitation on the Lokomat device (Hocoma AG, Volketswil, Switzerland) as the previous treatment group. In this case, the parameters for setting up the machine will be determined by the physiotherapist administering the patient’s specific characteristics. The effective treatment duration will be 30 min, considering a preparation time for the patient on the machine of approximately 30 min.

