### Fidelity to treatment and adverse events monitoring

To guarantee that an experienced research group member will train in the most accurate intervention, the physiotherapists involved in using the Lokomat and conventional gait will be tested, and their abilities will be tested.

At the beginning of the study, each physiotherapist will be provided with a form for recording the intervention specifications. Any unpredictable adverse event will be recorded in each patient’s registry and the study’s electronic database and managed according to the hospital’s policies, with referral for appropriate medical follow-up.

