### Statistical analysis

Descriptive statistics (mean and 95% CI) will be reported at T0, T1 and T2 for all the variables. The distribution of data at baseline will be tested using the Shapiro-Francia tests. The baseline comparison between the three groups will be performed using the χ^2^ test for categorical variables and one-way analysis of variance (ANOVA) or the Kruskal-Wallis test for continuous variables, as appropriate. The outcome comparison between the three groups will be performed using a one-way ANOVA or Kruskal-Wallis test according to sample distribution. The intragroup comparison between T0, T1 and T2 will be performed using a t-test for paired data or a Wilcoxon test, depending on the distribution. In case of imbalances at baseline between the groups, appropriate statistical correction analyses (eg, analysis of covariance) will be adopted. Patient perspectives on the acceptability and usability of the robot intervention will be analysed using descriptive analysis for quantitative and inductive content analysis for qualitative data.^56^

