## Discussion

This pilot randomised controlled trial aimed to investigate the efficacy of robot-assisted gait rehabilitation in PwMS by identifying the robotic intervention’s loading factors, related metabolic response and the patient’s perspective. Identifying these non-operator-dependent intervention models would optimise the use of RAGT in future research studies and clinical practice.

We expect this study to observe an improvement in gait, mobility and balance in all patients, both those who received robot-assisted gait rehabilitation and those who received OGT. However, considering the results of increasing training intensity in other populations,^16 19 23^ we expect significantly greater changes in subjects assigned to the low-intensity RAGT at progressively increasing intensity group than in the other treatment groups.

Identifying the optimal dose response could be useful in PwMS, where fatigue management must be considered when defining the rehabilitation intervention and its parameters. The novelty of the intervention we will apply lies in proposing a low-intensity intervention and gradually increasing its intensity throughout the treatment sessions. This approach seems in contrast to literature recommendations regarding exercise characteristics that must be intense and high doses to promote learning mechanisms and neuroplasticity.^57 58^ The idea that more is better may not be suitable for a patient in whom symptoms like fatigue and spasticity caused by high-intensity training may compromise the effectiveness and applicability of the intervention, particularly in patients with a high disability level. Furthermore, implementing a low-intensity protocol would broaden the range of PwMS who can benefit from robotic gait therapy.

Concerning exosomal urinary miRNAs, we expect to identify one or more miRNA correlated with MS to confirm that urine is a useful body fluid for detecting molecules related to this pathology. We also expect to be able to establish one or more miRNA panels to be used as diagnostic/prognostic biomarkers of the effects of treatments, regardless of the intervention.

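### The three-group test compares whole programmes, so it cannot alone answer the primary aim of relating response to imposed load

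*Protocol article*

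**What the plan says.** **Rationale and aim.** The Introduction cites an earlier study that expressed exercise intensity as average training speed relative to basal walking speed, as an objective measure of the load on the patient. In its RAGT group this ran from 11% to 114%, with "a significant inverse relationship between the relative intensity of exercise and the increase in walking speed at the end of rehabilitation". Aims of the study then makes it the primary aim to test whether "the variability of response to RAGT in PwMS might be related to the imposed load factors and the consequent metabolic response". The Discussion adds: "Identifying the optimal dose response could be useful in PwMS".

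**Treatments.** The low-intensity arm uses "a speed initially set at 1.0 km/hour, with progressive increments of 0.1 km/hour at each training session", at 60% assistance and 50% suspension, in eight bouts of 3 min with 1 min of recovery. In conventional RAGT, "the parameters for setting up the machine will be determined by the physiotherapist", with 30 min of effective treatment. Overground training includes a 40 min walk. Twelve sessions are planned, and the Intervention section says: "Patients who miss more than three rehabilitation sessions will be excluded from the study". On recording, "each physiotherapist will be provided with a form for recording the intervention specifications".

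**Analysis.** The Statistical analysis section says: "The outcome comparison between the three groups will be performed using a one-way ANOVA or Kruskal-Wallis test according to sample distribution". It also lists paired within-group tests, and analysis of covariance if the groups are unbalanced at baseline. None of these relates an outcome to load or to the metabolic measure.

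**The concern.** The aim asks how response depends on load. The printed test asks whether three programmes give different results. These are different questions, and two features of the treatments keep the second from answering the first.

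- The low-intensity speeds are absolute and the same for everyone, so a patient's relative speed in that arm depends on how fast he or she walks at baseline. The text gives no speed for conventional RAGT. The group label therefore does not tell a reader how far apart the two Lokomat arms were on relative speed.
- The programmes differ in several settings at once, so a group difference belongs to the package.

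At stake is how the result is read. A null result could mean that load does not matter, or that relative speed was similar in both Lokomat arms. A positive result could come from speed, assistance, suspension or the interval structure. In either case a statement about load or dose response would go beyond what the three-group test supports.

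**Working it through.** The protocol states no power or effect size and gives no sample size calculation, so there is no figure of its own to reproduce.

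**1. Speed schedule (low-intensity section).** Session k runs at 1.0 + 0.1 × (k − 1) km/h. Session 12 is at 2.1 km/h, and the mean is (1.0 + 2.1)/2 = 1.55 km/h. With nine sessions, the fewest that avoid exclusion, and if the increment counts attended sessions, the range is 1.0 to 1.8 and the mean is 1.40 km/h.

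**2. Baseline speed from the T25-FW.** 25 ft = 7.62 m. A time of t seconds gives 7.62 × 3.6/t = 27.43/t km/h.

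**3. Relative speed in the low-intensity arm.** Mean training speed / T0 speed:

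- 12 sessions: 155 × t/27.43 = 5.65% × t
- 9 sessions: 140 × t/27.43 = 5.10% × t

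| T25-FW at T0 (assumed) | 12 sessions | 9 sessions |
|---|---|---|
| 10 s | 57% | 51% |
| 15 s | 85% | 77% |
| 20 s | 113% | 102% |
| 30 s | 170% | 153% |

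With 12 sessions the mean passes 100% at 27.43/1.55 = 17.7 s.

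**4. Separation of the Lokomat arms.** For a given patient, a conventional speed averaging 1.55 km/h gives the same mean relative speed as the low-intensity schedule. At 2.1 km/h the low-intensity value is 1.55/2.1 = 74% of the conventional one. At 1.0 km/h it is 1.55/1.0 = 155% of it. The text does not say which case applies.

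**5. What else differs.** Work time is 8 × 3 = 24 min, 30 min and 40 min. Between the Lokomat arms, assistance, suspension and intervals are fixed in one and not specified in the other.

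**6. What a load-response analysis could detect.** For a two-sided 5% test with 80% power, z = 1.96 + 0.84 = 2.80. Detectable |r| = tanh(2.80/√(n − 3 − c)), where c is the number of covariates:

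- 16 Lokomat patients, no covariate: tanh(2.80/√13) = 0.65
- 16 patients, adjusted for T0 speed: tanh(2.80/√12) = 0.67
- 8 conventional RAGT patients, adjusted for T0 speed: tanh(2.80/√4) = 0.89

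**7. Information within the low-intensity arm.** With full attendance, log(load) = log(1.55) − log(T0 speed), so load and T0 speed have a correlation of −1 on the log scale. On the raw scale, with t uniform on 10 to 30 s, r = −0.96 and the variance inflation factor is 1/(1 − 0.96²), about 13. After adjustment for T0 speed, this arm adds almost nothing about load from within itself.

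**The case against.** The strongest defence is that the programme is a deliberate package. The aim speaks of load factors in the plural, and the low-intensity settings fix assistance, suspension and intervals as well as speed. Muscle oxygen consumption is measured at all three visits. A fixed schedule also serves the stated goal of an intervention that does not depend on the operator, and therapist-set RAGT is a legitimate comparator. All of this stands, and it is why the schedules should not change. It does not turn a comparison of packages into an analysis of load.

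Three further points also stand in part.

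- Figure 2, which plots velocity against time, is not available in the text reviewed and may show an intended contrast in speed. The conventional RAGT section still leaves the settings to the physiotherapist.
- The recording form probably captures speed, so the data are likely to exist.
- A load analysis may be in a fuller protocol or an analysis plan that is not shown. The point is therefore the mismatch between the printed aim and what the printed test can support, not the absence of detail.

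A reader might infer that the Lokomat arms will not differ on relative speed, or that the low-intensity arm is really a high-intensity one. The documents support neither. Conventional speeds and T25-FW times are not given, and assistance, suspension and rest also lower load. The percentages above may not be on the same scale as the earlier 11% to 114%, because the walking test used there is not named.

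**Conclusion.** The point holds as a mismatch between aim and analysis. The three-group comparison is a valid randomised test of programmes. Alone, it cannot show whether the two Lokomat arms differed on relative speed, and it cannot attribute a difference to load.

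This conclusion follows from the text and needs no outside figure. The 57% to 170% range does rest on an assumption, namely T25-FW times of 10 to 30 s, with full attendance and the T25-FW standing in for basal speed. How many patients lie at each level is unknown. With 8 per arm, chance differences in T0 speed can also widen or narrow the gap between the arms on relative speed.

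Severity is minor. The Discussion already says that a pilot of this size allows no definitive conclusions, and it mentions dose response as a motive rather than a promised result.

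**What to change.** Keep both Lokomat treatments as they are, and:

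1. Take the speed of every session from the intervention form for each patient in both Lokomat arms. Compute mean training speed / T0 T25-FW speed, and report it by arm beside the primary outcome.
2. In the Statistical analysis section, describe the three-group test as a comparison of programmes.
3. Add an exploratory regression of T25-FW response on delivered relative speed in the 16 Lokomat patients, adjusted for T0 speed. The adjustment is needed because T0 speed is both the denominator of load and the starting point of the response.
4. State its limits: 80% power needs |r| of about 0.67; the low-intensity arm adds almost no within-arm information after adjustment; speed is one of several load factors; and any difference in relative speed between the arms comes together with the other settings.

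The cost is one division per patient, one table column and one exploratory model, with no extra patients or visits. If forms already completed lack session speed, it must be recovered or reported as missing. The price in interpretation is a narrower, exploratory claim about load.
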